### Measurement tools

#### Anthropometric parameters and body composition

The anthropometric measurements will be performed at the outset of the fasting state by a trained nutritionist. In addition, bodyweight will be measured to the nearest 0.1 kg, with the participants in light clothing. The height of the subjects will be measured using a stadiometer in the standing position to the nearest 0.1 cm. BMI will be defined as the weight (kg) divided by the square of height (m^2^), and waist circumference will be measured at the midline between the iliac crest and lowest ribs to the nearest 0.5 cm. Finally, the body composition of the participants will be determined using bioelectrical impedance analysis (AVIS 333).

#### Dietary measurements

Dietary intakes will be assessed using the valid and reliable food frequency questionnaire [32], and the collected data will be expressed as gram per day using household measures. In addition, the modified food consumption database of the US Department of Agriculture will be used to calculate the daily nutrient intake of each subject [33].

#### Physical activity

The level of physical activity in the participant will be evaluated using a validated questionnaire [34] and calculated based on the metabolic equivalent tasks. Based on the questionnaire, the participants will be divided into three groups of low, medium, and high physical activity.

#### Screening questionnaires

A screening questionnaire will be designed based on a researcher-made questionnaire and the available standardized questionnaires in order to acquire the general data of the participants. Accordingly, the subjects will be excluded for medical reasons such as hypertension, CVDs, hypothyroidism/hyperthyroidism, intolerance, allergies, diabetes mellitus, and other acute/chronic diseases.

#### Indirect calorimetry

At this stage, the participants will be asked to stay awake and motionless in the supine position, and air samples will be collected using a mask (MetaLyzer 3B-R3 device). Moreover, respiratory gas exchange measurements will be recorded for 20 min in the fasting state, followed by hourly measurements for 6 h after the consumption of the test meals. Furthermore, fasting REE will be measured in a quiet area at room temperature, with the participants in the supine position. The respiratory quotient will also be calculated based on the oxygen consumption and carbon dioxide production, and TEF will be measured as the difference of the postprandial subtracted by the fasting REE. The resting energy expenditure and substrate utilization will also be estimated via indirect calorimetry after resting for 30 min.

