### Inclusion criteria

The inclusion criteria of the study are as follows: (1) age of 18–40 years; (2) adults with normal weight (body mass index [BMI]: 18.5–23.5 kg/m^2^, body fat percentage: 12–22%, waist circumference < 90 cm), and obese adults (BMI > 27.5 kg/m^2^, body fat percentage > 27%, waist circumference > 95 cm); (3) apparently healthy men; (4) written informed consent to participate; and (5) willingness to undertake the required fasting periods.

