### Test meals

Three interventions will be implemented in the current research, involving the consumption of high-fat, high-carbohydrate, and high-protein meals as the test meals in a randomized order. On the day of the intervention, the TEE of the subjects will be determined via indirect calorimetry. The test meals will contain 25% TEE for men, and the high-protein meal will consist of bread, cheese, boiled eggs, and skimmed milk (30% protein, 50% carbohydrates, and 20% fat). The high-carbohydrate meal will consist of skimmed milk, white bread, butter, jam, and honey (70% carbohydrates, 20% fat, and 10% protein), and the high-fat meal will contain bread, butter, cream cheese, high-fat milk, and jam (50% fat, 10% protein, and 40% carbohydrates). The subjects will be asked to ingest the test meals within a maximum of 15 min on each test day.

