#### Experimental protocol

The day before each of the three test days, the subjects will prepare their own meals and a standardized daily menu plan, which will consist of 15% protein, 55% carbohydrates, and 30% fat based on their daily energy requirements. The diets will ensure equally filled glycogen stores and similar macronutrient balance in each subject on every test day. The subjects will not be allowed to engage in severe physical activity within 2 days prior to the test days. On the test day, the subjects will arrive at the research center at Imam Reza Hospital at 7 AM with minimum activity (by car/bus) and after fasting from food, drinks (except water), caffeine, and alcohol for the past 12 h.

Before the tests, all the subjects will rest in the supine position for 30 min, lying on a bed in the semirecumbent position until the end of the tests. Initially, all the measurements will be performed in the fasting state and postprandially within 6 h. At the next stage, the participants will randomly receive the test meals and given 15 min to take the meals under the supervision of the researcher until the test meal is completely consumed. Afterwards, the participants will complete a series of tests, including indirect calorimetry, PWV, and pulse wave analysis. In addition, blood samples will be collected within 6 h. All the tests will be carried out in the exact same conditions (e.g., temperature-regulated room and quiet area). Following the test meals, the participants will fast again, refraining from food and drinks (except water) for another 6 h while the testing stage will continue. The testing conditions will be repeated on the next two test days. Figure 2 depicts the schedule of the study days.

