## Discussion

The current research aims to investigate the effects of the single ingestion of various test meals on the metabolic responses and vascular reactivity of healthy and obese adults. To the best of our knowledge, no previous research has concurrently assessed the postprandial effects of three meals with various compositions (high-protein, high-fat, and high-carbohydrate) on metabolic and vascular parameters. Based on the study design, the subjects will receive three types of meal on different test days to determine the differences in the metabolic parameters and arterial stiffness indices between the normal and obese subjects.

Considering the design of the present study, the balance in the confounding variables will be ensured in the study groups, and the bias induced by the characteristics of the subjects will be removed. However, the main challenge in this experiment will be the attrition rate and subject compliance as they must attend the study setting on three days, and the study process will continue for almost 7 h for each subject on each test day. Consequently, some of the subjects may fail to complete the three test days due to lengthiness, tardiness, and other reasons. Notably, the researchers will thoroughly describe the principles and requirements to the subjects prior to the experiment in order to ensure their compliance.

Conflicting results have been proposed regarding the effects of meal composition on metabolic and vascular responses. Based on the hypothesis of the current research, our findings will describe the effects of meal composition on metabolic and vascular responses. Given the increasing prevalence of CVDs and their close correlation with dietary habits, lipemia, and glycemia after meals, investigating the effects of meal composition on vascular functions and metabolic responses is of great interest. Furthermore, the subject matter may be incorporated into the design of novel lifestyle and dietary interventions. We recognize that in this pilot study, we are not powered to investigate effects between the different groups. Collecting data on the secondary outcomes such as metabolic and vascular responses will help to inform sample size calculations in future studies.

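### TEF is defined as an absolute difference while meals are scaled to each man's own expenditure, so the secondary lean-obese TEF comparison can reflect meal size

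*Protocol article*

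**What the plan says.** Test meals sizes the intervention to expenditure: "The test meals will contain 25% TEE for men". The quantity is the subjects' own: "On the day of the intervention, the TEE of the subjects will be determined via indirect calorimetry".

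Indirect calorimetry gives the outcome: "TEF will be measured as the difference of the postprandial subtracted by the fasting REE". Before the meal, the only calorimetry it describes is that "respiratory gas exchange measurements will be recorded for 20 min in the fasting state", with the participant supine and motionless. Hourly measurements over 6 h follow the meal.

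Experimental protocol adds a standardised menu on the day before each test day, set "based on their daily energy requirements".

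Inclusion criteria separate the groups on BMI (18.5–23.5 versus above 27.5 kg/m²) and on body composition: "body fat percentage: 12–22%, waist circumference < 90 cm" for normal weight, "body fat percentage > 27%, waist circumference > 95 cm" for obese.

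The Discussion says the three meals are given "to determine the differences in the metabolic parameters and arterial stiffness indices between the normal and obese subjects". The Abstract lists TEF among the postprandial effects. Outcomes makes the metabolic comparison secondary and ties it to sample size calculation. Statistical analysis names baseline tests and repeated-measures ANOVA. Nowhere is TEF expressed relative to meal energy or adjusted for it.

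**The concern.** The thermic response depends on how much energy is eaten. Under the stated meal rule, a man with higher expenditure eats more, and under the stated TEF definition that extra energy passes straight into the outcome. A lean-obese difference in TEF then mixes two things: a difference in thermic response per kcal, which is of interest, and a difference in meal size, which the design creates.

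The distortion can run either way. It can create a difference where the response per kcal is equal, or hide a lower response per kcal in obese men behind their larger meals.

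This is a pilot, but the comparison is not idle. Outcomes and Statistical analysis say the data will feed sample size estimation and the choice of outcome measure for the main study. The Conclusion makes the larger study depend on a significant result. A meal-size artefact in TEF could enter each of these decisions.

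A related difficulty is the quantity that sets the meal. Test meals names TEE by indirect calorimetry on the test day, while the only pre-meal recording described is a 20-minute resting one. The previous day's menu already needs a figure for daily requirements.

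**Working it through.** The article contains no calculation for TEF, so there is no figure to reproduce. The check is algebraic.

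**From the article:** meal energy = 0.25 × TEE (Test meals); TEF = postprandial minus fasting expenditure, unscaled (Indirect calorimetry); at least 12 men per group (Participants and data collection).

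**Assumed, not in the article:** the thermic response is a fraction f of meal energy, equal in both groups; lean TEE is 2400 kcal/day; the obese:lean TEE ratio r is 1.0 to 1.3.

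**Formula:** absolute TEF = f × 0.25 × TEE. With equal f, the obese:lean ratio of absolute TEF is r.

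**With f = 10%:** the lean meal is 0.25 × 2400 = 600 kcal and lean TEF is 60 kcal.

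| r | Obese meal (kcal) | Obese TEF (kcal) | Spurious difference | Obese TEF, % of meal |
|---|---|---|---|---|
| 1.0 | 600 | 60 | 0 | 10 |
| 1.1 | 660 | 66 | 6 kcal (10%) | 10 |
| 1.2 | 720 | 72 | 12 kcal (20%) | 10 |
| 1.3 | 780 | 78 | 18 kcal (30%) | 10 |

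The percentage excess depends only on r. In kcal, for r from 1.1 to 1.3, f from 8% to 15% and lean TEE of 2200 or 2400, the difference runs from 4.4 to 27 kcal. Divided by meal energy, TEF/(0.25 × TEE) = f in both groups, so the artefact is zero at every r.

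**Masking, same formula:** at r = 1.2, suppose the true response is 10% in lean men and 10%/1.2 = 8.33% in obese men. Absolute TEF is 0.10 × 600 = 60 kcal and 0.0833 × 720 = 60 kcal. A real difference per kcal disappears.

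**Size against noise (illustration only, since the article fixes no lean-obese test of TEF):** take 12 per group and an assumed between-man coefficient of variation of 25%. At r = 1.1, the pooled SD is √((15² + 16.5²)/2) = 15.8 kcal, giving a standardised difference of 6/15.8 = 0.38. At 1.2 and 1.3 it is 0.72 and 1.03. By noncentral t on 22 df, a two-sided 5% test would reject in 14.5%, 39.6% and 67.8% of trials with no true difference per kcal. For coefficients of variation from 15% to 40%, the range is 8.6% to 98.1%.

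**The case against.** The strongest reply is that the TEF sentence stands under Measurement tools and describes how the quantity is obtained. Whether it is reported in kcal or as a percentage of intake could be left to a fuller document. But the article does more than stay silent: it states a definition, and following it gives the distorted contrast.

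Second, TEF is part of a secondary outcome in a feasibility pilot that disclaims power for group effects, and no lean-obese test of TEF is specified. This stands and limits the severity. It does not remove the point, because the article intends the comparison and means to use the data for planning.

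Third, the size is wholly assumed. This also stands: no TEE by group is given, and entry at a BMI above 27.5 does not guarantee a large gap.

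Some stronger readings are not supported:

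- A reader might infer that glucose, insulin, free fatty acid and triglyceride responses are biased in the same way and need meal energy as a covariate. The algebra covers TEF only. Scaling meals to each man's needs is a legitimate design choice. Meal energy is also tied to group through TEE, so with 12 men per group the adjustment would remove part of the group contrast and rely on thin overlap. It is at most a sensitivity analysis.
- A reader might infer that resting expenditure will stand in for TEE, making meals a smaller share of TEE than stated. No section says so. Table 1 lists energy expenditure and resting metabolic rate separately at baseline, and schedules a physical activity questionnaire at time 0. The wording needs reconciling, but a substitution is not shown.
- A reader might infer that meals are resized at each visit and that this undermines the within-man contrasts. The text does not clearly say so. All three meals are 25% of the same man's TEE, so those contrasts are largely protected.

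**Conclusion.** The point holds for the lean-obese comparison of TEF. As written, the meal rule and the TEF definition together make the obese:lean ratio of absolute TEF equal to the TEE ratio whenever the response per kcal is the same. The spurious excess is about 10%, 20% or 30% at TEE ratios of 1.1, 1.2 or 1.3, and nil at 1.0.

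This rests on two assumptions: a thermic response proportional to meal energy, and a higher TEE in obese men. The second is expected from the inclusion criteria, but the article does not document it.

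The consequence is confined to a secondary outcome and the planning that uses it. The feasibility conclusions stand. The change should be made, but the point does not call the pilot into question. Separately, the article is not consistent on which energy quantity sets the meal and when it is obtained.

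**What to change.** In Indirect calorimetry, define TEF for the lean-obese comparison as:

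TEF (%) = 100 × (6-h postprandial energy expenditure − fasting REE over 6 h) / energy of the meal served.

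Show the absolute value as secondary. Record the energy served at each visit. Use the percentage form when TEF data inform the main study's sample size or choice of outcome for the lean-obese contrast.

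Reconcile Test meals, Indirect calorimetry and Experimental protocol, so that they agree on which energy quantity sets the meal, how it is obtained and when. Which quantity that should be is for the investigators to state.

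The cost is a few sentences and one division. Meal energy has to be known to prepare the meal, and the calorimetry is already scheduled, so no new measurement is needed.

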#### Pulse wave analysis

All the patients will receive an ultrasound examination of the carotid artery in the supine position, with the head turned to 45° from the side to be scanned and the operator placed on their right side. In addition, brachial blood pressure evaluation and pulse wave analysis will be conducted in the supine position using the Sphygmocor XCEL device. Blood pressure will be measured after the minimum rest of 15 min on the right upper arm in a quiet area. The augmentation index (AIx), central blood pressure (cBP), and heart rate (HR) will also be analyzed in accordance with the guidelines of the pulse wave analysis device manufacturer. After the measurement of the HR, cBP, and AIx will be estimated using built-in algorithms.

#### Carotid-radial PWV

Carotid-radial pulse wave velocity (PWV_b_) is a measure of arterial stiffness, which will be determined based on the sequentially measured electrocardiogram-gated left carotid and radial waveforms (applanation tonometry) using the foot-to-foot method to determine the pulse travel time in our study. Moreover, the travel distance of the pulse wave will be calculated as the difference in the distance between the suprasternal notch and each recording site using a tape measure over the body surface. The measurements will be performed at least twice, and the mean PWV_b_ will be applied to the analysis. PWV_b_ will be assessed at baseline and 30, 90, 150, 210, 270, and 330 min after the test meals.

#### Blood samples

Each test day will be implemented at 7 AM–2 PM; this period was selected since it was assumed to represent a common interval between breakfast and lunch. Serum samples will be collected before meal consumption and 60, 180, and 360 min after the meal initiation to evaluate metabolic activity markers. A maximum of 3 ml of the blood will be collected from each patient at each of the given times (12 ml/day) for the analysis of insulin, glucose, FFAs, TG, low-density lipoprotein, high-density lipoprotein, and total cholesterol. The blood samples will be collected at room temperature and immediately centrifuged, and the serum samples will be frozen at the temperature of −20 °C.

#### Experimental protocol

The day before each of the three test days, the subjects will prepare their own meals and a standardized daily menu plan, which will consist of 15% protein, 55% carbohydrates, and 30% fat based on their daily energy requirements. The diets will ensure equally filled glycogen stores and similar macronutrient balance in each subject on every test day. The subjects will not be allowed to engage in severe physical activity within 2 days prior to the test days. On the test day, the subjects will arrive at the research center at Imam Reza Hospital at 7 AM with minimum activity (by car/bus) and after fasting from food, drinks (except water), caffeine, and alcohol for the past 12 h.

Before the tests, all the subjects will rest in the supine position for 30 min, lying on a bed in the semirecumbent position until the end of the tests. Initially, all the measurements will be performed in the fasting state and postprandially within 6 h. At the next stage, the participants will randomly receive the test meals and given 15 min to take the meals under the supervision of the researcher until the test meal is completely consumed. Afterwards, the participants will complete a series of tests, including indirect calorimetry, PWV, and pulse wave analysis. In addition, blood samples will be collected within 6 h. All the tests will be carried out in the exact same conditions (e.g., temperature-regulated room and quiet area). Following the test meals, the participants will fast again, refraining from food and drinks (except water) for another 6 h while the testing stage will continue. The testing conditions will be repeated on the next two test days. Figure 2 depicts the schedule of the study days.

**Fig. 2 Fig2:**
[figure not shown]
Scheduling study days

## Discussion

The current research aims to investigate the effects of the single ingestion of various test meals on the metabolic responses and vascular reactivity of healthy and obese adults. To the best of our knowledge, no previous research has concurrently assessed the postprandial effects of three meals with various compositions (high-protein, high-fat, and high-carbohydrate) on metabolic and vascular parameters. Based on the study design, the subjects will receive three types of meal on different test days to determine the differences in the metabolic parameters and arterial stiffness indices between the normal and obese subjects.

Considering the design of the present study, the balance in the confounding variables will be ensured in the study groups, and the bias induced by the characteristics of the subjects will be removed. However, the main challenge in this experiment will be the attrition rate and subject compliance as they must attend the study setting on three days, and the study process will continue for almost 7 h for each subject on each test day. Consequently, some of the subjects may fail to complete the three test days due to lengthiness, tardiness, and other reasons. Notably, the researchers will thoroughly describe the principles and requirements to the subjects prior to the experiment in order to ensure their compliance.

Conflicting results have been proposed regarding the effects of meal composition on metabolic and vascular responses. Based on the hypothesis of the current research, our findings will describe the effects of meal composition on metabolic and vascular responses. Given the increasing prevalence of CVDs and their close correlation with dietary habits, lipemia, and glycemia after meals, investigating the effects of meal composition on vascular functions and metabolic responses is of great interest. Furthermore, the subject matter may be incorporated into the design of novel lifestyle and dietary interventions. We recognize that in this pilot study, we are not powered to investigate effects between the different groups. Collecting data on the secondary outcomes such as metabolic and vascular responses will help to inform sample size calculations in future studies.

## Conclusion

If a significant result is achieved regarding the measured parameters in the pilot study, we will design a study with a larger sample size consisting of both genders. The results of these studies may provide the proper tools to adapt various meal types to different body compositions in order to improve metabolic responses and vascular reactivity.

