#### Outcomes

The primary outcome will to evaluate the feasibility of conducting a trial to compare the effect of three test meals in lean and obese men. The feasibility will be assessed by measuring subject compliance with the intake of three test meals, recruitment, and retention rate in 3 days of study. Also, adherence to sample collection protocol will be assessed. Secondary outcomes will to compare the effect of three test meals on metabolic responses and vascular parameters in lean and obese men for sample size calculation.

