#### Feasibility outcomes

The feasibility of recruitment will be determined by calculating the proportion of enrolled participants from those screened for eligibility from the varied recruitment sources. Retention will be measured by the percentage of participants completing the study through the post-assessment. Intervention adherence will be measured from the information recorded by a nutritionist at three test days. The study will be deemed successful if (1) 60% recruitment target is achieved, (2) 80% or more of the subjects completed this study, and (3) subjects and investigators report acceptability of the study and adherence to the sample collection protocol will be reviewed by investigators.

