## Statistical analysis

Briefly, descriptive statistics will be used to summarize enrollment adherence, recruitment rates, and dropout. Feasibility outcomes will be presented as percentage and 95% confidence intervals. A retention rate of > 80% will be considered as feasible to conduct a future RCT. Analysis of outcomes will be conducted using both intention to treat. Also, in the analysis of clinical outcomes, descriptive statistics will be used to compare and determine the primary characteristics of the study groups, and the normal distribution of the variables will be evaluated using the Kolmogorov-Smirnov test. In total, 24 subjects have been assigned to the obese and normal groups. The baseline comparisons between the groups will be performed using the independent samples *t* test or Mann-Whitney *U* as appropriate. In addition, repeated-measures analysis of variance (ANOVA) will be used to assess the timing effect of the research parameters in various phases of the study. Data will be used for sample size estimation and to determine the most appropriate outcome measure for the main study.

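### The Conclusion ties design of the larger study to an undefined significant result, which conflicts with feasibility as the primary outcome and with the stated lack of power

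*Protocol article*

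**What the plan says.** The protocol article speaks about what follows the pilot in several places.

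- **Conclusion:** "If a significant result is achieved regarding the measured parameters in the pilot study, we will design a study with a larger sample size". The sentence adds that this study would include both sexes. It gives no parameter, contrast or significance level, and no feasibility condition.
- **Outcomes:** the section states "The primary outcome will to evaluate the feasibility of conducting a trial to compare the effect of three test meals in lean and obese men". It also makes the metabolic and vascular comparisons secondary and says that they serve sample size calculation.
- **Feasibility outcomes:** "The study will be deemed successful if (1) 60% recruitment target is achieved", at least 80% of the subjects complete, and "subjects and investigators report acceptability of the study and adherence to the sample collection protocol will be reviewed by investigators". No significance test is among these criteria.
- **Statistical analysis:** "A retention rate of > 80% will be considered as feasible to conduct a future RCT". The data are also to be used for sample size estimation and for choosing the outcome measure of the main study.
- **Discussion:** "We recognize that in this pilot study, we are not powered to investigate effects between the different groups". It repeats that the secondary outcomes are there to inform later sample size calculations.
- **Participants and data collection:** 12 men per group follows a pilot rule. The aim is a sufficiently precise pooled standard deviation; no effect size or power is given.

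**The concern.** The decision whether and how to go on is the main product of a feasibility pilot. Every section except the Conclusion bases it on feasibility and gives the clinical outcomes a planning role. The Conclusion instead makes the next study depend on a significance test, directly after a Discussion that says the pilot cannot support one for group differences.

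The two rules can disagree. A pilot that recruits and retains well may show nothing significant, and one that fails its feasibility criteria may still yield a significant result. The document does not say which rule prevails or whether both must be met. The significance rule also cannot be applied as written, because it does not say what must be significant.

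**Working it through.** **There is no plan figure to reproduce.** The article gives no alpha, power, effect size or standard deviation for the clinical outcomes. The only sample size arithmetic is 2 × 12 = 24.

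**Inputs from the document**
- 12 lean and 12 obese men (Research hypothesis and study time).
- All men eat all three meals (Experimental design), so meal contrasts are within-subject with up to 24 men.
- Parameters (Abstract, Table 1, Blood samples): resting energy expenditure, thermic effect of feeding, respiratory quotient, carbohydrate oxidation, fat oxidation, augmentation index, pulse wave velocity, glucose, insulin, free fatty acids, triglycerides, LDL, HDL and total cholesterol. That makes 14. It is 13 if substrate oxidation counts once and 15 if protein oxidation is added. Blood pressure and heart rate in Table 1 would add more.

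**Assumptions (not in the document)**
- Two-sided alpha of 0.05 per parameter, with no multiplicity adjustment.
- Standardised differences d = 0.5 to 0.8.
- Equal pairwise correlation rho between parameters, from 0 to 0.8.

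**Reading A: one given parameter must be significant, lean v obese**

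Two-sample t test, 22 degrees of freedom, critical value 2.074, noncentrality d × √(12/2).

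| d | Noncentrality | Power | Chance of missing it |
|---|---|---|---|
| 0.5 | 1.225 | 0.216 | 78% |
| 0.8 | 1.960 | 0.466 | 53% |

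Power of 80% needs d of about 1.20. With no true difference, the false go-ahead chance is 5%.

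**Reading B: any one of the parameters suffices, lean v obese**

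With no true effect and independent parameters, the chance of at least one significant result is 1 − 0.95^k:
- k = 13: 0.487
- k = 14: 0.512
- k = 15: 0.537

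Simulated with 14 correlated parameters, the chance of at least one significant result is:

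| rho | No effect (false go-ahead) | d = 0.5 on all 14 | d = 0.8 on all 14 |
|---|---|---|---|
| 0 | 51% | 97% | about 100% |
| 0.5 | about 35% | 72% | 93% |
| 0.8 | 20% | about 50% | 78% |

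The last two columns are the favourable case. Effects on fewer parameters would lower them.

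**Reading C: a within-subject meal contrast in all 24 men**

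Paired t test, 23 degrees of freedom, noncentrality dz × √24:
- dz = 0.5: noncentrality 2.449, power 0.65.
- dz = 0.8: noncentrality 3.919, power 0.96.

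If a plain change over time also counted, an expected rise in glucose after a meal could meet the condition. That says nothing about whether a larger trial is warranted.

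**Can feasibility alone carry the decision?** For the retention part, assume exactly 24 men are enrolled. Then 0.80 × 24 = 19.2, so at least 20 must complete. The two wordings of the threshold (80% or more; above 80%) agree at that number. The rate 20/24 = 83.3% has an exact 95% interval of 62.6% to 95.3%. That is imprecise, but it can be applied as written, which the significance rule cannot.

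**The case against.** The strongest reply is that the Conclusion is forward-looking prose and not a formal progression rule. It speaks of designing a larger study, not starting one. It does not say that a non-significant result ends the programme or that the feasibility criteria are set aside. The study it describes includes both sexes, whereas the trial whose feasibility is tested is in men, so the sentence may concern an extension. The Abstract says, without condition, that the pilot will inform a larger randomised trial. The two rules could also be cumulative: feasible, and with a signal.

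Much of this stands. A reader might infer that the main trial could start or stop by chance, with high error rates in both directions. The document does not support that, for three reasons:
- The sentence does not expressly start or stop a trial. If both conditions apply, an infeasible pilot could not go ahead on a chance p-value.
- The high false go-ahead rate (Reading B) and the low power for one given parameter (Reading A) belong to different rules. Under A the false go-ahead rate is 5%. Under B widespread effects are missed far less often. Taking the worse figure from each describes no single rule.
- The admission on power concerns effects between groups. Within-subject meal contrasts have more power.

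The conflict itself remains. A conditional commitment to a next study is naturally read as a go-ahead rule, and nothing says that it is cumulative. Even if it is, a feasible pilot could be held back by a comparison that the authors say is not powered.

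**Conclusion.** The point holds as an inconsistency between stated rules, and this does not depend on any assumed figure. The Conclusion conditions design of the larger study on undefined significance. That conflicts with feasibility as the primary outcome, the success criteria, the retention rule, the planning role of the clinical outcomes and the power statement in the Discussion.

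Its numerical size is conditional on the reading:
- **One given parameter:** 53% to 78% chance of missing a true lean-obese difference of d = 0.8 to 0.5, with a 5% false go-ahead rate.
- **Any of about 14:** about 20% (rho 0.8) to 51% (independent) false go-ahead. The independence figure is an upper end, since respiratory quotient and substrate oxidation come from the same gas exchange measurements.

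Alpha, effect sizes and correlations are assumptions. Severity is moderate: formal success criteria already exist, and the sentence changes no procedure, endpoint or sample size in the pilot.

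**What to change.** Replace the significance condition in the Conclusion. Suggested content: going on to a larger study will rest on the criteria under Feasibility outcomes and Statistical analysis; metabolic and vascular results will be reported as estimates with standard deviations and 95% confidence intervals, and used to plan its sample size.

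If the sponsor does want a clinical signal to count as well, the text should say that it is additional to feasibility and name the parameter, the contrast and the threshold.

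The cost is one sentence of wording. It needs no new data, visits or analyses.
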